### Study population

The study population will comprise individuals aged 18 to 60 years old who are diagnosed with MetS according to the Joint Interim Statement (JIS) on MetS definition of 2009 issued by the IDF Task Force on Epidemiology and Prevention; National Heart, Lung, and Blood Institute; American Heart Association; World Heart Federation; International Atherosclerosis Society; and International Association for the Study of Obesity [1].

According to the JIS definition [1], MetS is defined by the presence of at least three of five of the following risk factors:
WC: males ≥ 90 cm, females ≥ 80 cm (South Asian cut-points)BP: systolic BP ≥ 130 mmHg and/or diastolic BP ≥ 85 mmHg or receiving treatment for hypertension (HPT)FBG: ≥ 5.6 mmol/L or receiving treatment for elevated glucoseTG: ≥ 1.7 mmol/L or receiving treatment for TGHigh-density lipoprotein cholesterol (HDL-c): males < 1.0 mmol/L, females < 1.3 mmol/L or receiving treatment for HDL-c

### Patient recruitment

Consecutive patients who attend the university primary care clinic during the recruitment period will be approached, given the patient information sheet about the study, and invited to participate. Those who are willing to participate will be interviewed and screened by the investigators to identify eligibility on the basis of inclusion and exclusion criteria. Written informed consent will be obtained from those who are eligible, and they will be recruited into the study.

### Inclusion criteria

Patients 18 to 60 years old who fulfil all of the following inclusion criteria will be included:
Diagnosed with MetS according to the JIS definition [1]Have received follow-up care for MetS at the university primary care clinic at least twice in the last 1 yearHave regular access to the internetPerceive that they have basic skills to use the web and smart mobile phoneAre able to read and understand written English or Malay

### Exclusion criteria

Patients who fulfil any of the following criteria will be excluded:
Type 1 diabetes mellitusReceiving renal dialysisPresent with severe hypertension (systolic BP > 180 mmHg and/or diastolic BP > 110 mmHg) at recruitmentDiagnosed with conditions resulting in secondary hypertensionDiagnosed with circulatory disorders requiring referral to secondary care over the last 1 year and during the course of the study (e.g., unstable angina, heart attack, stroke, transient ischaemic attacks, peripheral vascular diseases)Receiving shared care at primary and secondary care centres for CVD (coronary artery diseases, stroke, transient ischaemic attacks, peripheral vascular diseases)Receiving chemotherapy/radiotherapy or palliative careDiagnosed with a psychiatric illness such as schizophrenia, bipolar disorder, major depressionDiagnosed with cognitive impairment such as dementiaPregnantEnrolled in another intervention study

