### Monitoring the intervention

During the 6-month intervention period, patients are required to use the EMPOWER-SUSTAIN self-management mobile app for a cumulative period of 2 h and be seen at least once by the PCPs for follow-up care. A separate web interface will be created for PCPs to monitor patients’ log-in frequency and duration of use of the tool. Patients who do not comply with the use and follow-up requirements will be considered as lost to follow-up. Patients who are lost to follow-up or who withdraw from the trial will not be replaced. Analysis will be by intention to treat (ITT). There is no other specific concomitant care and intervention that are permitted or prohibited during the trial.

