#### Effectiveness analysis

ITT analysis will be applied to measure the potential effectiveness of the EMPOWER-SUSTAIN Self-Management e-Health Intervention on the primary and secondary outcome measures based on the initial treatment assignment. Mixed model repeated measures analysis of variance will be carried out to evaluate the potential effectiveness (i.e., to compare the mean changes in patient activation, PA, diet, patients’ chronic illness care, and patient–physician interaction satisfaction scores) with regard to perceived absolute 10-year CVD risk within and between the intervention and control groups at baseline and 6-month follow-up.

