### Data monitoring

Data monitoring will be done by the EMPOWER-SUSTAIN investigators. Data on any adverse event or unintended effect of trial intervention or trial conduct will be collected, assessed, reported and managed by the investigators. An external data monitoring committee is not needed, because the intervention does not involve a new pharmacological agent or regulated device.

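### One exclusion criterion runs on through the study, so read literally it removes randomised patients on a post-randomisation event and conflicts with the promised ITT analysis

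*Protocol article*

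**What the plan says.** Under Exclusion criteria, the protocol article introduces the list with "Patients who fulfil any of the following criteria will be excluded". One entry is a diagnosis of "circulatory disorders requiring referral to secondary care over the last 1 year and during the course of the study", with heart attack and stroke among its examples. Another entry, severe hypertension, is tied explicitly to the time of recruitment.

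Under Patient recruitment, those willing to take part are "screened by the investigators to identify eligibility on the basis of inclusion and exclusion criteria", and written consent is taken afterwards from those found eligible.

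Two sections commit to ITT. Monitoring the intervention states it, next to the rule "Patients who are lost to follow-up or who withdraw from the trial will not be replaced". Effectiveness analysis applies it "on the primary and secondary outcome measures based on the initial treatment assignment".

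Under Data monitoring, "Data on any adverse event or unintended effect of trial intervention or trial conduct will be collected". Cardiovascular events are neither the primary outcome nor a secondary outcome.

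**The concern.** An eligibility criterion should be decidable when eligibility is decided. Nobody can know at screening whether a patient will be referred for a circulatory disorder later in the study. That half of the criterion can therefore act only after enrolment, and for most of its span only after randomisation.

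If site staff apply it as worded, a randomised patient who has such an event stops being a trial patient. Two things are then at stake.

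- **The analysis set.** Membership would depend on a post-baseline event in an unblinded trial, and an ITT label cannot restore 6-month data that were never collected. A heart attack or stroke could plausibly change blood pressure and perceived cardiovascular risk, so these patients need not resemble the rest on the secondary outcomes.
- **The retention rate.** It is a named feasibility output for the later definitive trial. Exclusions created by the protocol itself would be mixed with real drop-out, and the wording could be carried into that trial.

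**Working it through.** **1. The passages side by side**

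| Question | Section | Answer given |
|---|---|---|
| When is eligibility judged? | Patient recruitment | At screening, before consent |
| What period does the criterion cover? | Exclusion criteria | The past year and the whole study |
| What follows from meeting it? | Exclusion criteria | Exclusion, without saying from what |
| Who is analysed? | Monitoring the intervention; Effectiveness analysis | ITT, "based on the initial treatment assignment" |
| What if a randomised patient meets the criterion later? | None | Not addressed |

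The second and third rows, taken literally, contradict the fourth. The open-ended window is not a general style of the list, because severe hypertension is confined to recruitment.

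**2. The plan's own figure**

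Inputs from Sample size determination: δ = 3.93, σ = 9.70, two-sided α = 0.05, power 0.80, 1:1 allocation.

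- Normal approximation: n = 2(1.96 + 0.8416)² × (9.70/3.93)² = 2 × 7.849 × 6.092 = 95.6, so 96 per group.
- t-test version: 96.6, so 97 per group. The stated 97 is reproduced.
- After the planned 20% drop-out from 116 per group: 116 × 0.80 = 92.8.

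**3. Patients affected**

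The article gives no event rate. Assume 1–3% over the study:

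- 232 × 0.01 = 2.3
- 232 × 0.03 = 7.0

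This is about 2 to 7 patients in all, or 1.2 to 3.5 per arm (116 × 0.01 and 116 × 0.03).

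**4. Shift in the primary comparison**

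Take an unfavourable case: one arm loses 3% of its patients and the other loses none. Assume that those lost differ from the rest of their arm by 5 PAM points.

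- Shift = 0.03 × 5 = 0.15 points.
- Against the design difference: 0.15/3.93 = 3.8%.
- Against the standard deviation: 0.15/9.70 = 1.5%.
- If the assumed difference is doubled to 10 points: 0.03 × 10 = 0.30 points.

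**5. Power**

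Power = Φ(δ/(σ√(2/n)) − 1.96), with n = 92.8 × (1 − r) per group, where r is the further fraction excluded.

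| r | Patients of 232 | n per group | Power |
|---|---|---|---|
| 0 | 0 | 92.8 | 78.8% |
| 0.5% | 1.2 | 92.3 | 78.6% |
| 1% | 2.3 | 91.9 | 78.4% |
| 2% | 4.6 | 90.9 | 78.0% |
| 5% | 11.6 | 88.2 | 76.7% |

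The loss is about 0.2 to 2 percentage points over this range.

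**6. Retention**

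If the excluded patients would otherwise have been retained and are counted as lost, retention falls by 1 to 3 percentage points, for example from the planned 80% to between 79% and 77%. If they are instead struck from the denominator, the rate describes a different population. The article does not say which applies.

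**The case against.** The strongest reply is that no section says these patients leave the analysis. The criteria are applied at screening, two sections state ITT, and the exclusion list is silent on analysis. The word for exclusion could mean only that the trial intervention stops, in which case ITT survives. This stands in part: removal from the analysis is the literal reading but not the only one. It does not clear the text. The article nowhere gives the milder reading, and the rule on patients who are lost or withdraw does not cover those who meet an exclusion criterion mid-study.

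A second reply is that the clause may be meant for the interval before treatment. Trial status plans recruitment for September to October 2020, baseline data from December and the intervention from January 2021, with no date for randomisation. Part of the window could therefore fall before randomisation. That is a reason to limit the criterion to that period rather than simply strike the words. The words as they stand still run to the end of the study.

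A third reply concerns two stronger conclusions that a reader might draw.

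- **That the cardiovascular events themselves would vanish from the trial's data.** The documents do not support this. Data monitoring covers any adverse event and makes no exception for these patients, and an event has to be known before it can trigger the criterion. What could be lost is these patients' 6-month questionnaires and measurements.
- **That removal would differ between arms.** Intervention patients have arranged visits at 3 and 6 months with physicians trained on guidelines, so earlier diagnosis or referral is conceivable. But both arms come from regular follow-up at one clinic, visits are unlimited in both, and a heart attack or stroke is seldom discovered at a self-management visit. A difference is possible, not shown.

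Finally, the numbers affected are small beside the 20% drop-out already allowed, about 23 per arm (116 × 0.20 = 23.2). That is right, and it limits the severity.

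**Conclusion.** The point holds as a conflict in the stated text. The exclusion criterion reaches past randomisation, and read literally it is incompatible with ITT by initial assignment. The exposure is loss of 6-month PAM-13-M and secondary outcome data in the affected patients, and an unclear retention rate. It is a question of who is followed and analysed, not of sample size.

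The size is small. At an assumed event rate of 1–3%, 2 to 7 of 232 patients are involved. The primary comparison moves by about 0.15 points if one arm alone loses 3% and those patients differ by 5 points. The event rate and the 5-point difference are assumptions without a source in the article.

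Severity is minor to moderate. A higher grade would need evidence of lost adverse events or of unequal removal, and the article supports neither. It is still worth settling before enrolment, because outcome data not collected at 6 months cannot be recovered.

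**What to change.** Reconcile Exclusion criteria with Monitoring the intervention and Effectiveness analysis:

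- Limit the circulatory-disorder criterion to the time before randomisation. This keeps any intended cover for the gap between recruitment and allocation.
- Add one sentence: a randomised patient who has such an event later stays in 6-month outcome collection and in the ITT analysis, and counts in the denominator for retention.

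Whether such a patient continues the intervention, and the patient's clinical care, is for the investigators and is not touched by this change. If the clause was meant as a rule on stopping the intervention, it should be stated as such, outside the eligibility list.

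The cost is a few words changed and one sentence added. No change to sample size or visits is needed.

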### Physician recruitment

All primary care physicians (PCPs) who are practicing at the university primary care clinic will be invited to participate in the study. To be eligible, the following criteria must be met:
Have one or more years of working experience in a primary care settingMust be keen to participate in the studyWilling to deliver the EMPOWER-SUSTAIN e-Health Intervention to patients with MetS

At least ten PCPs who meet the eligibility criteria will be recruited. Five PCPs will be allocated to deliver the EMPOWER-SUSTAIN intervention, and the rest of the PCPs will continue with usual care.

### EMPOWER-SUSTAIN Self-Management e-Health Intervention

The EMPOWER-SUSTAIN Self-Management e-Health Intervention is a complex intervention involving multifaceted components using CCM as the conceptual framework [11, 12]. This is in line with the United Kingdom Medical Research Council (MRC) complex intervention framework, which recommends that intervention development be guided by best available evidence and an appropriate framework [46, 47]. A comprehensive review of the literature was conducted to identify the crucial components of the EMPOWER-SUSTAIN intervention that could improve patient activation and self-management behaviours. Three crucial components were identified on the basis of three CCM elements (i.e., delivery system design, self-management support and decision support) and will be included in the EMPOWER-SUSTAIN Self-Management e-Health Intervention as described in Table 1. Figure 2 illustrates the conceptual framework underpinning the EMPOWER-SUSTAIN Self-Management e-Health Intervention.

**Table 1 Tab1:** EMPOWER-SUSTAIN Self-Management e-Health Intervention

Chronic Care Model elements	Crucial components	Intervention
Decision support	Decision support for physicians to translate CPG recommendations into day-to-day clinical practice [48–50]	EMPOWER-SUSTAIN Training Workshop for PCPs to use web-based desktop and mobile applications and to reinforce the use of relevant CPG for management and prescribing
Self-management support	Self-management support to facilitate patient activation and behaviour change [51–54]	PCPs to support and empower patients with knowledge, skills and confidence in using the EMPOWER-SUSTAIN mobile application and the EMPOWER-SUSTAIN Global CV Risks Self-Management Booklet using the persuasive technology approach
Delivery system design	Delivery system design through the EMPOWER-SUSTAIN clinic to improve continuity of care and patient–physician relationship [55–57]	The EMPOWER-SUSTAIN Self-Management e-Health Intervention will be delivered by PCP at baseline and 3-month and 6-month follow-up visits in the EMPOWER-SUSTAIN clinic to ensure continuity of care and sustainability

*CPG* Clinical practice guidelines, *PCP* Primary care physician

**Fig. 2 Fig2:**
[figure not shown]
The conceptual framework for the EMPOWER-SUSTAIN Self-Management e-Health Intervention

### Development of the EMPOWER-SUSTAIN self-management mobile application

The EMPOWER-SUSTAIN web-based self-management mobile application is currently at the final stage of development. The iterative model was chosen as the software development model for this study [58]. Content from the newly revised EMPOWER-SUSTAIN Global Cardiovascular Risks Self-Management Booklet was evaluated for its suitability to be included in the prototype. A storyboard was designed to create the flow of prototype use by PCPs, nurses and patients during follow-up in the clinic and at home. In the pre-alpha stage, wireframe was designed to describe and visualise the user interface in static draft layouts based on the content and structure of information. Based on the wireframe, high-fidelity mock-up static graphic diagrams demonstrating the content and function of the prototype divided into eight sections were designed. The sections included My Profile, My Cardiovascular Risks, My Treatment Targets, My Check-Up, My Weight Management, My Smoking Habit, My Self-Management, and My Medication. Persuasive technology theory [39, 59] was used to build the evidence-based content, which is presented in a user-friendly interface, with incorporation of interactivity and a reward system. This app is designed to aid and motivate people to adopt a positive attitude and behaviour change through persuasion and a reward system. The EMPOWER-SUSTAIN mock prototype mobile app is provided in Additional file 2. Based on the mock graphic diagrams, a working prototype of the EMPOWER-SUSTAIN self-management mobile app was developed using the iterative model of the Software Development Life Cycle [58, 60]. A complementary desktop application is also being developed for the PCPs and nurses to use in the clinic. This prototype is currently undergoing alpha (utility) testing by medical experts [61, 62] and beta (usability) testing by patients with MetS [63]. Data which are entered by the PCPs and patients into the app will be stored in a secure server. The feasibility of using the app will be evaluated in this pilot study.

### Conduct of the EMPOWER-SUSTAIN Workshop

Prior to the delivery of the intervention, the five PCPs in the intervention arm and a nurse will be trained on how to use the EMPOWER-SUSTAIN desktop and mobile applications during the EMPOWER-SUSTAIN Workshop. Training will also include reinforcing the use of relevant clinical practice guidelines (CPG) [64] as decision support for management and prescribing. The PCPs and nurse will be trained on the basis of Self-Determination Theory (SDT), which would be useful for them to understand how patients’ behaviour change can be influenced by health care providers [65]. They will also be trained in motivational interview (MI) techniques and health-coaching skills to facilitate patients’ autonomous self-regulation to enhance their behaviour change [65–68]. MI training would include the skills to formulate open-ended questions, reflective statements (i.e., restating what the patients conveyed) and stimulating what the patients know before providing relevant education [65]. The main aim of the MI is to engage patients in problem solving by encouraging active learning [66] and facilitating patients’ autonomous self-regulation to achieve goals by enabling patients to develop individualised action plans [67, 68].

### Delivery of the intervention

The EMPOWER-SUSTAIN Self-Management e-Health Intervention will be professionally delivered to the individual patients by the PCPs, assisted by a nurse. Patients will be given the EMPOWER-SUSTAIN self-management app, which will be downloaded to their mobile phone. Follow-up care by the PCPs will be arranged at baseline, 3 months and 6 months. At baseline, patients in the intervention arm will be given a username and password to access the app. They will be trained individually on its use by the PCPs assisted by a nurse using the Knowledge to Action (KTA) Framework [69] and the persuasive technology theory [39, 59]. The KTA Framework incorporates the need to adapt the knowledge to fit with individual context. In addition to this, PCPs and the nurse will provide problem-solving assistance and support for patients to use the app in line with the theory of persuasive technology. MI techniques and health-coaching skills to facilitate patients’ autonomous self-regulation to enhance their behaviour change will also be applied. PCPs and the nurse will go through each section with the patients and will ensure that information recorded in all sections is complete. Patients will be guided to navigate through the functions of the mobile app to ensure competence, especially on the sections involving self-management. Patients will be coached to use the app and to review their progress at home (e.g., self-monitoring of their weight, BP and blood glucose) and recording of their PA and diet. Particular attention will be given to specific pages of the app which summarise patients’ achievement in their self-management goals and clinical outcomes. These achievements will be rewarded with a star rating in accordance with the persuasive technology theory. PCPs and the nurse will discuss self-management progress and goals using the app with the patients at each follow-up visit. The goal of the intervention is to improve patient activation and self-management behaviours through patient–physician collaboration and regular reinforcement to ensure sustainability. Figure 3 illustrates the delivery of the EMPOWER-SUSTAIN Self-Management e-Health Intervention.

**Fig. 3 Fig3:**
[figure not shown]
Delivery of the EMPOWER-SUSTAIN Self-Management e-Health Intervention

### Monitoring the intervention

During the 6-month intervention period, patients are required to use the EMPOWER-SUSTAIN self-management mobile app for a cumulative period of 2 h and be seen at least once by the PCPs for follow-up care. A separate web interface will be created for PCPs to monitor patients’ log-in frequency and duration of use of the tool. Patients who do not comply with the use and follow-up requirements will be considered as lost to follow-up. Patients who are lost to follow-up or who withdraw from the trial will not be replaced. Analysis will be by intention to treat (ITT). There is no other specific concomitant care and intervention that are permitted or prohibited during the trial.

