### Control group

The control group will continue to receive usual care at the university primary care clinic. They will be given the EMPOWER-SUSTAIN Global CV Risks Self-Management Booklet, as this is considered as usual care at the university primary care clinic. The EMPOWER-SUSTAIN self-management mobile app will be made available to the control group at the end of the study. During the course of the study, there will be no limit to the number of clinic visits that a patient is allowed to make in either the intervention or control group. Figure 4 shows the EMPOWER-SUSTAIN schedule of enrolment, interventions and assessments according to SPIRIT guidelines [40].

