### Feasibility outcomes

Process evaluation to assess the integrity of the randomised controlled trial protocol will be conducted. These include recruitment rate, methods of randomisation, retention rate, appropriateness of the primary and secondary outcome measures, sample size calculation, whether the intervention could be delivered as intended, and methods of statistical analysis to evaluate the potential effectiveness. Qualitative studies to explore facilitators and barriers in delivering the intervention among PCPs and using the intervention among patients will also be conducted. However, detailed methods for the qualitative studies are beyond the scope of this paper.

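### Low app use is labelled as loss to follow-up, in effect in the intervention arm only, which mixes adherence with retention and conflicts with the intention-to-treat analysis

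*Protocol article*

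**What the plan says.** The rule is in the protocol article under Monitoring the intervention. Over the 6 months, "patients are required to use the EMPOWER-SUSTAIN self-management mobile app for a cumulative period of 2 h and be seen at least once" by the physicians. The consequence of falling short is then given: "Patients who do not comply with the use and follow-up requirements will be considered as lost to follow-up". The next sentence says that patients lost to follow-up or withdrawn are not replaced, and the one after that commits the trial to intention to treat (ITT).

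Four other places bear on the rule:

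- **Control group:** "The EMPOWER-SUSTAIN self-management mobile app will be made available to the control group at the end of the study". Delivery of the intervention issues log-in details at baseline to the intervention arm only.
- **Outcome measures:** outcomes are to be obtained in both groups at baseline and 6 months, with no exception for low users.
- **Effectiveness analysis:** "ITT analysis will be applied to measure the potential effectiveness" of the intervention "on the primary and secondary outcome measures based on the initial treatment assignment".
- **Feasibility outcomes:** the items to be evaluated include "recruitment rate, methods of randomisation, retention rate, appropriateness of the primary and secondary outcome measures". Study setting says that the pilot should support safe assumptions about effect size, recruitment and retention in the definitive trial.

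**The concern.** Loss to follow-up normally means that the outcome was not obtained. Here it is defined by what the patient did with the treatment after randomisation. A patient who used the app for 90 minutes and completes the activation questionnaire at 6 months is lost under one section and evaluable under another.

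Two things are at stake. The first is the retention rate. Counted by this rule, it measures attendance plus app use in one arm and cannot measure the same thing in the other. The definitive trial would inherit a wrong drop-out rate and an artificial imbalance between arms.

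The second is the effect estimate. App use plausibly follows motivation, and the primary outcome measures self-reported knowledge, skills and confidence for self-management. If the label led staff not to measure low users, or the analyst to drop them, a more activated subset of the intervention arm would be compared with the whole control arm.

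**Working it through.** **Inputs from Sample size determination.** Target difference 3.93 points, SD 9.70, two-sided 5% level, 80% power, 97 per group before drop-out, 20% drop-out, 116 per group recruited.

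**The plan's own figure.** The normal approximation gives n = 2 × (1.960 + 0.842)² × 9.70² / 3.93² ≈ 95.6, so 96. The exact two-sample t test gives 96.6, so 97, with power 80.2%. The stated 97 is reproduced. The point itself concerns a definition and does not depend on this figure.

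**Inputs not in the document (assumptions).** The share of intervention patients failing the requirement, f, is taken as 10 to 40%. The shortfall of low users in mean activation change, D, is taken as 2 to 6 points.

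**Retention as recorded.** Suppose all 232 patients attend at 6 months and retention is counted by the stated rule. Recorded retention is 1 − f in the intervention arm and 100% in control.

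| f | Intervention | Control | Overall |
|---|---|---|---|
| 10% | 90% | 100% | 95% |
| 20% | 80% | 100% | 90% |
| 30% | 70% | 100% | 85% |
| 40% | 60% | 100% | 80% |

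With 20% genuine attrition in both arms and f = 20% among those remaining, the intervention arm records 0.80 × 0.80 = 64% against 80% in control. If loss means no 6-month outcome, both arms record 100% in the first case and 80% in the second.

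**Effect estimate, only if labelled patients are left out.** Assume no true effect, SD 9.70 and 20% other, non-selective drop-out in each arm, which leaves 116 × 0.80 = 92.8 per arm. A fraction f of the remaining intervention patients is then removed. The mean of that arm rises from (1 − f) × m(users) + f × m(low users) to m(users), so:

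bias = f × D

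SE = 9.70 × √(1/(92.8 × (1 − f)) + 1/92.8)

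For f = 0.20, the intervention arm has 74.2 patients and SE = 9.70 × √(1/74.2 + 1/92.8) ≈ 1.51. Then:

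- **D = 3:** bias 0.6 points, or 0.6/3.93 = 15% of the target. The standardised shift is 0.6/1.51 ≈ 0.40, and two-sided rejection is Φ(−1.56) + Φ(−2.36) ≈ 6.8%.
- **D = 5:** bias 1.0 point, or 25% of the target. The standardised shift is 1.0/1.51 ≈ 0.66, and rejection is Φ(−1.30) + Φ(−2.62) ≈ 10.2%.

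Over the whole assumed grid (f from 10 to 40%, D from 2 to 6 points), the bias runs from 0.2 to 2.4 points and the type I error from about 5% to 31%. The width of that range shows how far the result depends on inputs that the document does not give.

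**The case against.** A reader might infer that low users are removed from the analysis and that the rule therefore cannot coexist with ITT. The text does not go that far. The only consequence it attaches to the label is that these patients are not replaced. ITT is stated directly afterwards, and 6-month outcomes are planned in both groups. The sections can be read together: low users are labelled, not replaced, and still measured and analysed as randomised. On that reading the effect estimate is protected and only the retention figure is at risk.

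Other parts of the objection also have force:

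- The text does not say whether failing one requirement or both triggers the label, and the visit requirement could be read as covering controls. Only the app-use part is clearly one-sided.
- The threshold is low: 120 minutes over about 26 weeks is under 5 minutes a week. Participants must report internet access and basic skills, and they are trained individually. Nothing in the document supports a failure rate as high as 40%.
- Because the protocol counts low users as lost, its 20% drop-out allowance may already include them. Removing them on top of it implies a total intervention-arm loss of 1 − 0.8 × 0.8 = 36% at f = 20%.
- Feasibility outcomes does not say that retention will be counted from this label, and it lists delivery as intended as a separate item.

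These points make the bias figures conditional. They do not rescue the sentence. It is an explicit definition that conflicts with the usual meaning of loss and with the analysis principle beside it, not detail left to another document. No section says that labelled patients still give outcome data or stay in the analysis, and no other definition of loss is offered for the retention rate.

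**Conclusion.** The rule is wrong as written. It turns an adherence criterion into loss to follow-up, and its app-use part can be failed in one arm only. Applied to the retention rate, it understates intervention-arm retention by the share of low users among those who attend: 80% against 100% if that share is 20%. This follows from the definition; only the share is assumed.

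The label also conflicts with ITT and with 6-month outcome collection in both arms. Exclusion is what the label would ordinarily suggest, but it is not stated, so bias in the treatment comparison is a risk and not a planned feature. For illustration, its size is 0.6 to 1.0 points (15 to 25% of 3.93) with a type I error of about 7 to 10%. That rests on actual exclusion, no true effect, 20% other drop-out in each arm, 20% of the remaining intervention patients removed, and a 3 to 5 point shortfall among them. The larger figures at 40% removal have no support in the document.

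**What to change.** Replace the sentence under Monitoring the intervention with three statements:

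1. In both arms, a patient is lost to follow-up only if no 6-month outcome is obtained. The retention rate is counted on this definition.
2. All randomised patients are invited to the scheduled 6-month assessment and analysed as randomised, regardless of app use or visits.
3. Meeting the 2 h and one-visit requirement is reported separately as an adherence (feasibility) outcome, saying whether one or both parts must be met. Any analysis restricted to compliers is labelled as a sensitivity analysis.

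The cost is a short change of wording, plus inviting low users to an assessment that is already scheduled. The estimated effect may be smaller than one based on adherent patients only.
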